### Histopathological analysis

Quantitative analysis of the fibroblasts of the keloid specimens will be performed. For such, the histological slides with the samples will be stained with hematoxylin-eosin (H.E.). An analysis of collagen fibers will also be performed using additional slices stained with Picrosirius Red and RNA extraction will be performed for the analysis of TGF-β.

### Statistical analysis

The Kolmogorov-Smirnov test will be used to determine the normality of the data. Variables with parametric distribution will be submitted to one-way analysis of variance (ANOVA) followed by Tukey’s test for comparisons between groups. Variables with nonparametric distribution will be submitted to the Kruskal-Wallis test followed by Dunn’s post hoc text for comparisons between groups. The significance level will be set at α = 5%.

Original study forms will be entered and kept on file at the participating site. When a form is selected, the participating site staff will pull that form, copy it, and sent the copy to the data coordinating center. Participants’ files will be stored in numerical order and stored in a secure and accessible place and manner. They will be maintained in storage for a period of 05 years after completion of the study. The primary author will be responsible for the database on its own device and in the storage cloud. He has no conflicts of interest and no funding.

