### Sample size and participants

The sample size was calculated considering a significance level of 0.05 and 80% power to obtain the means of improvement at three months postoperatively using the Vancouver Scar Scale (corticoid group: mean = 1.95; SD = 1.84) based on the paper by HEWEDY *et al*. [63]. Due to the lack of data in the literature regarding the study group, we estimated the same variability found in Group 1 (G1 1.95 vs. G2 0.25, difference of 1.7). Considering a 10% dropout rate, a total of 58 participants will be recruited: N = 29 per group. All participants will be recruited from the Mandaqui Hospital Complex and Nove de Julho University as well as through announcements in digital media.

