### Randomization of groups

Block randomization will be performed using a sequence generator program (Research Randomizer, version 4.0, computer software available since June of 2013 at http://www.randomizer.org). The participants will be assigned sequential numbers (1–58). Each patient is going to be allotted an opaque envelop which will contain a piece of paper stipulating to which group it belongs. The envelopes will be sealed until the time of the treatment and their contents will be determined randomly. The patients will be randomly allocated to two groups:The participants will be assigned sequential numbers (1–58). Each patient is going to be allotted an opaque envelop which will contain a piece of paper stipulating to which group it belongs. The envelopes will be sealed until the time of the treatment and their contents will be determined randomly. The patients will be randomly allocated to two groups:

Study group (N = 29): intralesional administration of corticoid and active photobiomodulation in the preoperative and postoperative periods of keloid surgery.Sham group (N = 29): intralesional administration of corticoid and sham photobiomodulation in the preoperative and postoperative periods of keloid surgery.

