## Evaluations

### Questionnaires

A questionnaire will be administered to the participants to collect their personal information. The determination of skin phototype will performed using the Fitzpatrick classification [64] prior to the onset of the interventions in the participant’s first outpatient appointment by trained health professionals and students.

The *Quality of Life of Patients with Keloid and Hypertrophic Scarring* [5] questionnaire, which has been translated and validated for Portuguese, as well as the *QualiFibro/Plastic Surgery—UNIFESP* questionnaire [65] will be used for the assessment of quality of life. The participants will answer the questionnaires prior to the intervention as well as one, three, six, and twelve months postoperatively. The participants will also answer Part II (classification of satisfaction) of the *Patient Scar Assessment Questionnaire* (PSAQ) [66], which has been translated and validated for Portuguese [67], for the assessment of the quality of the remaining scar one, three, six, and twelve months postoperatively. These questionnaires will be applied in the same way in the periods already explained by trained health professionals and students.

Blinded, calibrated, certified plastic surgeons will answer the *Vancouver Scar Scale* (VSS) [68], which was translated into Portuguese by Santos et al. [69], after the clinical evaluation prior to the intervention as well as one, three, six, and twelve months postoperatively.

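### One-way ANOVA with Tukey (or Kruskal-Wallis with Dunn) does not fit two arms measured at baseline and four later visits: the post hoc step is empty, baseline is unused, and the month-3 contrast is not named

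*Protocol article*

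**What the plan says.** The Statistical analysis section gives one rule for all variables. After a normality test: "Variables with parametric distribution will be submitted to one-way analysis of variance (ANOVA"), with Tukey's test for comparisons between groups. Variables that fail the normality test go to Kruskal-Wallis with Dunn's test. The section names no visit, patient effect or baseline term.

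The design is described elsewhere in the protocol article:

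- Randomization of groups: "The patients will be randomly allocated to two groups".
- Questionnaires: surgeons score the VSS "after the clinical evaluation prior to the intervention as well as one, three, six, and twelve months postoperatively". Quality of life follows the same schedule. The PSAQ is given only at the four postoperative visits.
- Measurement of keloid and remaining scar: molds are taken preoperatively and at the same four visits.
- Histopathological analysis: fibroblasts, collagen and TGF-β are measured on the keloid specimens.
- Sample size and participants: the trial is sized on "means of improvement at three months postoperatively using the Vancouver Scar Scale", with "significance level of 0.05 and 80% power".

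**The concern.** Tukey's and Dunn's tests sort out which of three or more groups differ. With two arms there is nothing to sort out. The post hoc step therefore either does nothing, or it signals that groups means something other than arms, and the text does not say which.

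One-way ANOVA and Kruskal-Wallis also treat all observations as independent and take no covariate. Most outcomes here are repeated on the same patients, and several have a pre-treatment value.

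At stake is whether the primary comparison is fixed in advance. The sample size rests on one contrast at one visit, but the analysis text does not identify it, so the same data could be analysed in ways with quite different error rates and power.

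**Working it through.** **Inputs from the document.** Control group: "corticoid group: mean = 1.95; SD = 1.84". Effect: "G1 1.95 vs. G2 0.25, difference of 1.7". For the study group's SD, "we estimated the same variability found in Group 1". Dropout is 10%, with 29 per arm. Two-sided testing is assumed, since sidedness is not stated. Completers per arm: 29 × 0.9 = 26.1, taken as 26.

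**Assumed, because the document gives no value.** Within-patient correlation between visits (ρ) of 0.3, 0.5 and 0.7; baseline-outcome correlation (r) of 0.1, 0.3 and 0.5.

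**Step 1: the plan's own figure.** n per arm = 2 × [(1.96 + 0.84) × 1.84 / 1.7]² = 18.4, so 19 (20 with the t distribution). After 10% dropout this is 22 to 23, not 29. The stated 29 is matched at 90% power (26 by t-test; 26 / 0.9 = 28.9). This mismatch is a separate matter and does not affect the point here. It does mean that sample size is not the constraint.

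**Step 2: two arms compared at one visit (the literal reading).**
- Standard error = 1.84 × √(2/26) = 0.510. Noncentrality = 1.7 / 0.510 = 3.33.
- The t-test critical value at 50 df is 2.009. Power is 90%.
- Tukey's critical value for two groups, q/√2 at 50 df, is also 2.009. The post hoc step changes nothing.
- Each test holds its 5% level. If all four postoperative visits are tested with none singled out, the chance of at least one false positive is 18%, 16% or 13% at ρ = 0.3, 0.5 or 0.7 (simulation, 10,000 null trials). With independent visits it would be 1 − 0.95⁴ = 18.5%.

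**Step 3: arm-by-visit cells as the groups (not stated in the document).**
- Ten cells: q(0.95; 10, 250) = 4.51, so |t| must exceed 4.51/√2 = 3.19. Power for the month-3 contrast at noncentrality 3.33 is about 56%.
- Eight cells (baseline left out): |t| > 3.06, power about 61%.
- The between-arm contrast at a given visit compares different patients, so its standard error is not distorted by within-patient correlation when variances are equal. In simulation, any false between-arm finding over the four postoperative visits occurred in 0.6% to 0.7% of null trials. The contrast is conservative. The independence assumption fails for the omnibus F test and for contrasts between visits.

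**Step 4: all four postoperative visits stacked by arm (not stated in the document).**
- The variance of an arm mean is understated by the factor 1 + 3ρ, so type I error ≈ 2 × [1 − Φ(1.96/√(1 + 3ρ))].

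| ρ | 1 + 3ρ | Formula | Simulation |
|---|---|---|---|
| 0.3 | 1.9 | 15.5% | 15.7% |
| 0.5 | 2.5 | 21.5% | 22.1% |
| 0.7 | 3.1 | 26.6% | 26.9% |

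**Step 5: what baseline adjustment would add.** Adjustment multiplies the residual variance by 1 − r². Taking 1.84 as the SD of the analysed outcome, with 26 per arm:

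| r | 1 − r² | Power |
|---|---|---|
| none | 1 | 90% |
| 0.1 | 0.99 | 91% |
| 0.3 | 0.91 | 93% |
| 0.5 | 0.75 | 96% |

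**The case against.** The strongest reply is that the plain reading is sound. The Statistical analysis section speaks of comparisons between groups, and the groups are defined as the two arms. One-way ANOVA of two arms at one visit is a t-test: unbiased under randomisation, at its nominal level, and with 90% power against the stated 80%. Within-patient correlation plays no part in it. For histology and TGF-β, measured on the removed keloid, the test is acceptable as it stands. All of this stands.

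A reader might infer from the Tukey step that a ten-cell ANOVA is intended, or that visits will be pooled, and conclude that the planned analysis is invalid. The document does not support that. It describes neither analysis, and a post hoc test may simply be standard wording. Nor would the cell ANOVA give wrong standard errors for the between-arm contrast at a visit; it would be conservative there.

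The case for using baseline is also modest. Baseline VSS and molds describe a keloid that is then excised with a margin of healthy skin, and later visits describe the surgical scar, so the correlation may be low. The sample size text speaks of improvement, so baseline might be meant to enter as a change score, though the analysis text does not say so. Whether 1.84 is the SD of a score or of a change is unclear.

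The reply leaves three things unanswered: a post hoc step with no function, four visits with no primary one named in the analysis, and no stated use of the baseline or of the repeated structure.

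**Conclusion.** The stated method does not fit the design and leaves the primary comparison open, but its most natural reading is valid. On that reading the cost is a redundant post hoc step, a small and uncertain loss of precision (90% power against 91% to 96% for r of 0.1 to 0.5), and a 13% to 18% chance of some false positive if four visits are tested without a named primary.

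The larger figures, power of about 56% and type I error of about 16% to 27%, show what could follow if the wording were carried out in two other ways. They belong to two different analyses, neither stated in the document, and should not be cited as properties of the plan.

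The results rest on 26 completers per arm, two-sided testing, equal SDs of 1.84, and the assumed correlations. The finding of misfit does not depend on the correlations. Severity: should-fix.

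**What to change.** Replace the ANOVA/Tukey and Kruskal-Wallis/Dunn sentences with text that does the following:

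- Names the arm difference in VSS at month 3, with its 95% confidence interval, as the primary contrast, in line with the sample size section.
- Analyses repeated outcomes with a mixed model for repeated measures: arm, visit, arm-by-visit, and within-patient covariance.
- Adjusts for the baseline value where one is collected (VSS, quality of life, area and volume). The PSAQ has no baseline, so its model omits that term.
- Keeps a rank-based or ordinal alternative for outcomes that are clearly non-normal.
- Uses a two-sample comparison for histology and TGF-β.
- Drops the Tukey and Dunn steps.

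The cost is wording and slightly more programming. No new data or patients are needed: with 26 completers per arm the unadjusted comparison already has about 90% power, and adjustment should not materially reduce it.

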## Interventions

### Intralesional administration of corticoid

The participants in both groups will receive an intralesional injection of 20 mg/ml triamcinolone hexacetonide (Triancil^®^, Apsen Farmacêutica S.A.)–two injections in the preoperative period with a two-week interval between injections and a monthly injection for three months in the postoperative period. The injections will be intralesional and will not surpass the dermis. The drug will be diluted with the same quantity of 2% lidocaine. The scar will be divided into equal parts of 1 cm^2^ and the drug will be distributed equally, respecting the total dose per session of 20 mg for the face and 40 mg for other topographies.

### Photobiomodulation protocol

PBM will be administered in four sessions with a two-week interval between sessions preoperatively as well as immediately after surgery, weekly in the first month postoperatively, at two-week intervals in the second month, and a single session in the third month. The light source will be blue LED (Quantum, Ecco^®^) using the parameters listed in Table 1. In the sham group, the light will be the same color but without power and, consequently, without any biological effect.

**Table 1 pone.0263453.t001:** Dosimetric parameters of photobiomodulation protocol.

Dosimetric parameters	Type of source: LED
Central wavelength [nm]	470
Operating mode	Continuous
Mean radiant power [W]	0.4
Aperture diameter [cm]	1.7
Power density at aperture [W/cm^2^]	0.17
Beam spot on target [cm^2^]	2.268
Irradiance on target [W/cm^2^]	0.176
Useful exposure time [s]	Varying according to size of scar, 60 s per linear cm. Ex.: 1 c m = 60 seg; 10 cm = 600 s.
Exposure time [s]	60 per linear cm
Energy density at aperture [J/cm^2^]	10.58
Radiant energy [J]	Varying with size of scar, according to duration of useful exposure (Item 9). Ex.: 1 cm = 4 J; 10 cm = 240 J
Energy per point [J]	4J
Application technique	Contact
Anatomic location of application points	On remaining scar
Number and frequency of treatment sessions	Preoperative: every two weeks for 30 days. Postoperative: Immediately after surgery, weekly for 4 weeks, every two weeks for another 4 weeks, and one session in 3^rd^ month.

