## Abstract

Keloid scars are characterized by the excessive proliferation of fibroblasts and an imbalance between the production and degradation of collagen, leading to its buildup in the dermis. There is no “gold standard” treatment for this condition, and the recurrence is frequent after surgical procedures removal. *In vitro* studies have demonstrated that photobiomodulation (PBM) using the blue wavelength reduces the proliferation speed and the number of fibroblasts as well as the expression of TGF-β. There are no protocols studied and established for the treatment of keloids with blue LED. Therefore, the purpose of this study is to determine the effects of the combination of PBM with blue light and the intralesional administration of the corticoid triamcinolone hexacetonide on the quality of the remaining scar by Vancouver Scar Scale in the postoperative period of keloid surgery. A randomized, controlled, double-blind, clinical trial will be conducted involving two groups: 1) Sham (n = 29): intralesional administration of corticoid (IAC) and sham PBM in the preoperative and postoperative periods of keloid removal surgery; and 2) active PBM combined with IAC (n = 29) in the preoperative and postoperative periods of keloid removal surgery. Transcutaneous PBM will be performed on the keloid region in the preoperative period and on the remaining scar in the postoperative period using blue LED (470 nm, 400 mW, 4J per point on 10 linear points). The patients will answer two questionnaires: one for the assessment of quality of life (Qualifibro-UNIFESP) and one for the assessment of satisfaction with the scar (PSAQ). The team of five plastic surgeons will answer the Vancouver Scar Scale (VSS). All questionnaires will be administered one, three, six, and twelve months postoperatively. The keloids will be molded in silicone prior to the onset of treatment and prior to excision to assess pre-treatment and post-treatment size. The same will be performed for the remaining scar at one, three, six, and twelve months postoperatively. The removed keloid will be submitted to histopathological analysis for the determination of the quantity of fibroblasts, the organization and distribution of collagen (picrosirius staining), and the genic expression of TGF-β (qPCR). All data will be submitted to statistical analysis.

**Trial registration:** This study is registered in ClinicalTrials.gov (ID: NCT04824612).

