### Blinding

The evaluator, analyst, and participants will be unaware of the group to which the participants are allocated. The operator will also be unaware of whether the blue light has a biological or is a placebo effect.

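### The sham is defined as light of the same colour with no power, which, read literally, conflicts with the stated blinding of operator and participants and leaves the control exposure unstated

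*Protocol article*

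**What the plan says.** The sham is defined in one sentence of the protocol article, under Photobiomodulation protocol: "In the sham group, the light will be the same color but without power and, consequently, without any biological effect".

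The Blinding section makes two claims that depend on that sham. The first is "The evaluator, analyst, and participants will be unaware of the group to which the participants are allocated". The second is "The operator will also be unaware of whether the blue light has a biological or is a placebo effect". The second presumes that blue light is seen in both arms. The abstract and the Study design section call the trial double-blind.

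Table 1 describes one configuration, the active one: "Mean radiant power [W] 0.4", "Beam spot on target [cm^2^] 2.268", "Irradiance on target [W/cm^2^] 0.176", applied in contact, with exposure time given as "Varying according to size of scar, 60 s per linear cm". It has no sham entry.

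Under Questionnaires, participants rate their own quality of life and their satisfaction with the scar (PSAQ Part II). The Vancouver Scar Scale (VSS) is completed by blinded, calibrated plastic surgeons.

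**The concern.** Visible light carries radiant power. A source that emits none has no colour to show, and a source that shows blue emits some. Taken at face value, the sham sentence therefore asks for two things that do not go together at the probe tip, and each way of resolving it damages a different claim in the article.

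- **No output at the tip.** The active probe glows blue and the sham probe does not. Anyone who can see the treated site can tell them apart, against the statements in the Blinding section.
- **Some visible blue light at the skin.** The control arm receives an exposure that the article does not quantify. The article infers the lack of biological effect from the lack of power, so that inference loses its premise.

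Both arms receive the same corticoid schedule and the same surgery, so active versus sham light is the only planned difference. If participants work out their allocation, the outcomes they rate themselves could be biased, and no analysis can repair that afterwards.

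**Working it through.** **Inputs from the article.** Power 0.4 W, beam spot 2.268 cm², irradiance 0.176 W/cm², energy density 10.58 J/cm² and 60 s per linear cm (all Table 1); 29 patients per arm (Randomization of groups). No power, irradiance or energy is given for the sham beyond the statement that it has no power.

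**Step 1: reproduce the active figures.**
- Irradiance = power / area = 0.4 / 2.268 = 0.176 W/cm², as stated.
- Energy density for 60 s = 0.4 × 60 / 2.268 = 10.58 J/cm², as stated.

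The active configuration is therefore a sound reference for power and irradiance. The abstract's "blue LED (470 nm, 400 mW, 4J per point on 10 linear points" does not agree with 0.4 W × 60 s = 24 J per linear cm. That is a separate inconsistency, and this point does not depend on it.

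**Step 2: sham with literally zero output.** Energy = 0 × 60 = 0 J, with irradiance 0 against 0.176 W/cm² in the active arm. The sham tip shows no blue light, so the same-colour property and the operator-blinding statement both fail.

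**Step 3: sham with some output.** Let f be the fraction of active power that reaches the skin. The article gives no f, so the values below are assumptions, for scale only. Energy per 60 s = f × 0.4 × 60; energy density = that / 2.268.

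| Assumed f | Energy per 60 s (J) | Energy density (J/cm²) |
|---|---|---|
| 0.1% | 0.024 | 0.011 |
| 1% | 0.24 | 0.106 |
| 5% | 1.2 | 0.529 |
| 10% | 2.4 | 1.058 |

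Every row is above zero. The Introduction mentions inhibitory effects at higher energy densities (up to 640 J/cm²) but gives no level below which blue light is inert. The article therefore offers no basis for calling any row active or inactive.

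**Step 4: how often it arises.** Postoperative sessions are 1 + 4 + 2 + 1 = 8. Preoperatively, the text gives four sessions, and Table 1 (every two weeks for 30 days) can be read as three. That makes 11 to 12 sessions per patient. The two preoperative descriptions must themselves be reconciled.

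**Step 5: who is exposed.**
- *Operator:* handles the probe and may treat both arms, so can compare devices. Exposed whether the sham is dark or only faintly lit.
- *Participants:* each sees one device only and has no reference brightness. Exposed mainly if the tip is dark.
- *VSS surgeons:* described as blinded, and nothing says they attend light sessions.
- *Mould, histology and qPCR:* not patient-rated.

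**The case against.** The strongest reply is that the sentence is loosely worded rather than wrong. Both sections speak of blue light in both arms, so the intended meaning is probably light without therapeutic output. This is plausible as intent, but it does not remove the problem. Unless the light is kept from the skin, that reading leaves a control exposure with no figure, and a tip visibly fainter than a 0.4 W source can still be told apart by an operator who handles both.

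A second reply is that a journal article may leave the construction of the sham to a full protocol. That is right for filters, device coding and eyewear, and their absence is not the finding. The article does, however, define the sham and state who is blinded, and these two statements do not fit together.

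Several stronger conclusions are tempting, and the article does not support them:

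- *That such a sham cannot be built.* A probe with a lit housing and a blocked aperture would show blue and deliver nothing to the skin. The article does not describe such a device, but it is possible.
- *That the VSS is compromised.* It is scored by blinded surgeons, so only indirect disclosure by a patient or operator would reach it.
- *That participants would recognise a dimmer tip.* In a parallel-group trial they have nothing to compare it with.
- *That leaked light dilutes the treatment effect materially.* The leakage fractions above are assumed, and nothing in the article ties exposures of that size to an effect.
- *That sham patients would drop out, or that the two institutions would deliver different shams.* Both arms receive corticoid and surgery, and the article does not say that both institutions deliver the light sessions.

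**Conclusion.** The point holds in limited form. As written, the sham definition and the blinding statements conflict, and the claim of no biological effect rests on a zero output that a visibly blue tip would contradict. The contrast is 0 against 0.176 W/cm² if the sham is dark, and an unstated non-zero exposure if visible light reaches the skin. It would concern the 29 sham patients at each of 11 to 12 sessions.

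The likely consequences are loss of operator blinding under either reading and, if the tip is dark, possible bias in the patient-rated quality-of-life and PSAQ outcomes. The VSS and the mould and laboratory outcomes are less exposed. The verdict assumes that the sham has no feature, such as a blocked aperture behind a lit housing, that the article leaves undescribed. Because the actual harm depends on the device, this should be fixed, but it does not by itself invalidate the design.

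**What to change.** 1. Reconcile the sham sentence under Photobiomodulation protocol with the Blinding section by describing the device actually used as sham. Report its measured output at the skin, zero or otherwise, beside Table 1. This asks for a statement of fact; no level is proposed here.
2. Have participants wear the same light-blocking eyewear at every session in both arms, and the operator too where the procedure allows.
3. If the operator can still distinguish the devices, withdraw the operator-blind claim and keep the operator out of outcome collection, including administering the questionnaires.
4. Optionally, ask participants and operators to guess the allocation at the end of treatment and report the result.

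The cost is eyewear, one power-meter reading and a few sentences of text, and possibly a less favourable blinding statement than the present one.

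### Table 1 gives 4 J per point, but its own power and exposure time give 24 J, so the active light dose is uncertain by a factor of six

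*Protocol article*

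**What the plan says.** The section Photobiomodulation protocol refers to Table 1 for the parameters of the blue LED. The entries that matter here are:

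- Power: "Mean radiant power [W] 0.4", with "Operating mode Continuous".
- Exposure time: "Varying according to size of scar, 60 s per linear cm. Ex.: 1 c m = 60 seg; 10 cm = 600 s". A second row repeats 60 s per linear cm.
- Geometry: "Aperture diameter [cm] 1.7", with a beam spot of 2.268 cm² and an irradiance on target of 0.176 W/cm².
- Energy density: 10.58 J/cm².
- Radiant energy, said to vary with scar size through the exposure time: "Ex.: 1 cm = 4 J; 10 cm = 240 J".
- Energy per point: 4 J.

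The Abstract summarises the treatment as "470 nm, 400 mW, 4J per point on 10 linear points" and gives no exposure time.

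**The concern.** For a continuous source, energy is power multiplied by time, so these rows are not independent of each other. The radiant energy row fails on its face: going from 1 cm to 10 cm, the exposure rises 10-fold (60 s to 600 s) while the stated energy rises 60-fold (4 J to 240 J).

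Both arms receive the same corticoid and the same surgery, and the sham device shows the same colour without power. The light dose is thus the only planned difference between the arms. If it is not fixed, two things follow:

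- An operator who works to 4 J per point and one who works to 60 s per cm give doses that differ sixfold. If both happened within the active arm, the treatment contrast would be blurred.
- Even with uniform delivery, a report that repeats the published parameters would leave readers unable to tell which dose had been tested.

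The Introduction ties the inhibitory effect of blue light on fibroblasts and TGF-β to higher energy densities, so the value delivered bears on the hypothesis. It also determines how much exposure participants receive.

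**Working it through.** **Inputs** (all from Table 1): power P = 0.4 W, continuous; time t = 60 s per cm; aperture diameter d = 1.7 cm; spot area A = 2.268 cm²; energy density 10.58 J/cm²; 240 J for 10 cm. The Abstract gives the same power, 400 mW.

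**Step 1. Reproduce the entries that agree.**

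- Area = π(d/2)² = π × 0.85² = 2.270 cm² (stated 2.268).
- Irradiance = P/A = 0.4/2.268 = 0.176 W/cm² (stated 0.176).
- Energy density = P·t/A = 24/2.268 = 10.58 J/cm² (stated 10.58).
- Energy for 10 cm = 0.4 × 600 = 240 J (stated 240).

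**Step 2. Energy per point, by three routes.**

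- Power × time: 0.4 × 60 = 24 J.
- Energy density × area: 10.58 × 2.268 = 24.0 J.
- Stated 10 cm total divided by 10: 240/10 = 24 J.

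The stated value is 4 J, and 24/4 = 6.

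**Step 3. What would have to change for 4 J to be right.**

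- At 0.4 W, the time would be 4/0.4 = 10 s, not 60 s.
- Over 60 s, the power would be 4/60 = 0.067 W, not 0.4 W.
- The energy density would be 4/2.268 = 1.76 J/cm², not 10.58.
- Ten points would total 10 × 4 = 40 J, not 240 J.

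| | Following 4 J per point | Following 60 s per cm |
|---|---|---|
| Seconds per point at 0.4 W | 10 | 60 |
| Energy per point (J) | 4 | 24 |
| Energy density (J/cm²) | 1.76 | 10.58 |
| Energy for a 10 cm scar (J) | 40 | 240 |

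The table treats one point as one linear cm, as its own 1 cm example does.

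**Step 4. Look for a reading that reconciles them.** Pulsing is excluded because the mode is continuous. Several points per cm are excluded because 4 J is stated for 1 cm as well as per point. Damage in reading the table is unlikely, because 4 J stands in two rows of Table 1 and again in the Abstract, and the neighbouring entries are intact and agree with each other. No reading was found that reconciles the figures.

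**The case against.** The strongest reply is that the table does not offer two equally supported doses. Power, mode, irradiance, exposure time, energy density and the 10 cm total all lead to 24 J. The radiant energy row itself makes energy depend on exposure time, and the time instruction is explicit and consistent. An exposure of 10 s appears nowhere. On this view, operators will time 60 s per cm, the delivered dose will be 24 J, and only a label is wrong, perhaps through a dropped digit. Nothing in the document shows operators choosing a dose by joules, and no exposure limit is cited that either dose would breach. The ten points in the Abstract may simply carry over the 10 cm example.

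Much of this stands. 24 J is the better-supported value, mixed delivery is a risk and has not been shown, and the document gives no ground for calling either dose unsafe. The mention of ten points adds little on its own.

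The contradiction remains, however. The dropped digit is an inference, and 4 J is repeated three times. The Abstract gives watts, joules and points but no seconds, so anyone working from it would arrive at 10 s per point.

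**Conclusion.** The concern holds. Table 1 and the Abstract state 4 J per point, while the table's own power, time, spot area, energy density and 10 cm total give 24 J. The discrepancy is exactly sixfold: 1.76 against 10.58 J/cm² per point, and 40 against 240 J for a 10 cm scar. The result needs only a continuous source, which the table states, and no outside figure. Which dose is intended cannot be settled from the document, although most entries favour 24 J. The harms from mixed delivery depend on what operators actually do. The error leaves the randomisation, sample size and outcomes untouched, but it concerns the one factor that the trial tests, so it should be corrected before further treatment.

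**What to change.** The sponsor should confirm the intended dose and then:

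- Reconcile power, seconds per point, energy per point, energy density, total energy and number of points into one consistent set, in Table 1 and in the Abstract. If 24 J is intended, the three 4 J entries change. If 4 J is intended, the exposure time (or the power), the energy density and the 10 cm total change.
- State in the Abstract that the number of points follows scar length, or state in Table 1 that it is fixed at ten.
- Record delivered seconds and energy on the session form at every session.
- If any participant has already been treated, document which version that participant received.

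The cost is a correction to one table and the Abstract, plus a line on the session form.
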